### Coronary computed tomography angiography

At each participating centre, two independent experienced radiologists, blinded to patient data (especially the allocated harvesting cohort) [but not to the type of graft (LITA/RA/RITA/SVG) and their target vessels], will evaluate the cCTA results according to graft patency status. Graft status will be analysed for all bypass grafts. Graft patency by cCTA will be determined and classified as 1 = patent, 2 = dysfunctional and 3 = 100% occlusion.

In case of equal assessment of graft status by the 2 independent radiologists, no further assessment is necessary. In case of unequal assessment, cCTA image data will be sent anonymized as a DICOM file to the core centre. The cCTA will be assessed by a third experienced radiologist [blinded to patient data (especially allocated harvesting cohort) but not to the type of graft (LITA/RA/RITA/SVG) and their target vessels] at the core centre. This is considered as the final evaluation.

In cases with inconsistent results and if asked by the core centre, invasive angiography will be performed.

Cardiac computed tomography angiography will be performed in each centre using a CT scanner with ≥ 64 slices. At the Medical University Innsbruck, a 128-slice dual-source CT (Definition FLASH or DRIVE, Siemens Healthineers, Erlangen, Germany) with a detector collimation of 2 × 64 × 0.6 mm and a rotation time of 0.28 s will be used, together with high-pitch (3.2) scanning (Flash mode). Scans will be triggered into arterial phase using bolus tracking (threshold of 100 HU, ascending aorta) and by injecting an intravenous iodine contrast agent [iopromide (Ultravist 370), Bayer Healthcare, Berlin, Germany, 70–120 ml, depending on the patient’s body mass index]. Prospective electrocardiography triggering will be applied, and images will be reconstructed at an end-diastolic phase (70% of the RR-interval). Thinslice images will be reconstructed with a 0.75-mm slice width (increment, 0.4) and transferred to three-dimensional postprocessing software (SyngoVIA, Siemens Healthineers, Erlangen, Germany) for cCTA image analysis. Estimated radiation exposure will be 1–3 mSv.

Beta blockers may be given to lower the patient’s heart rate, pending on the centre’s individual internal guidelines (scanner-specific), prior to the scan. Patients will be advised not to drink coffee prior to the CT examination (in order to avoid an increase in heart rate).

### Outcome definitions

LITA graft occlusion in cCTA: absence of contrast detection in the lumen of the graft, indicating a 100% occlusion of LITA graft in cCTA;LITA graft dysfunction in cCTA: suspicion of LITA graft dysfunction in cCTA, either anatomical [anatomical stenosis ≥ 50% (for example, due to plaques, stricture) at anastomotic site or in the course of the graft], functional (due to competitive flow) or unclear (diffuse small-sized vessel without clear anatomical obstruction);LITA graft occlusion in CAG: complete occlusion (100%) of the LITA graft;LITA graft dysfunction in CAG: ≥ 50% stenosis of the LITA graft, string sign of the graft due to competitive flow or graft spasm;Intraoperative LITA graft injury: surgeon’s decision not to use LITA as a conduit after the harvesting process;MACE: composite outcome of all-cause death, myocardial infarction and repeated revascularization;All-cause death: death from any cause (cardiac or non-cardiac) from the time of the surgical procedure;Cardiac death: death due to myocardial infarction, cardiogenic shock, sudden cardiac death or cardiac arrhythmias;Non-cardiac death: death from any cause other than cardiac (e.g. cancer, trauma, pulmonary embolism);Myocardial infarction: composition of periprocedural myocardial infarctions and non-periprocedural myocardial infarctions;Periprocedural myocardial infarction during CABG: defined as type 5 myocardial infarction according to the criteria of the 4th universal definition of myocardial infarction [25];Spontaneous myocardial infarction: defined as types 1–3 myocardial infarctions according to criteria of the 4^th^ universal definition of myocardial infarction [25];Repeat revascularization: any form of repeat revascularization [CABG, percutaneous coronary intervention (balloon angioplasty or stent implantation)] after the index operation;Target vessel repeat revascularization: any form of repeat revascularization [CABG, percutaneous coronary intervention (balloon angioplasty or stent implantation)] to the LAD after the index operation;Sternal wound complication: superficial or deep sternal wound infection requiring external vacuum therapy, surgical treatment including wound debridement, open vacuum-assisted therapy or sternal reconstruction with concomitant antibiotic therapy;Perioperative mortality: death within 30 days after the primary surgery.

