### Secondary outcomes

MACE-free survival (composite outcome of all-cause death, myocardial infarction and repeated revascularization) within 1 year, 2 years and 5 years after surgery.

Additional secondary outcomes include the following:

Death/LITA graft occlusion (in cCTA or invasive angiography)/intraoperative LITA graft injury within 2 years (+/- 3 months) postoperatively;LITA graft occlusion (and LITA graft dysfunction) in cCTA or invasive angiography at 2 years (+/- 3 months);LITA graft occlusion at cCTA or invasive angiography for patients with cCTA or invasive angiography for clinical reasons;Repeated revascularization at 2 years and 5 years after surgery;Repeated revascularization of the left anterior descending artery (LITA target vessel revascularization) at 2 years and 5 years after surgery;Sternal wound complications at 1 year after surgery;Composite end point of the LITA graft occlusion/dysfunction (cCTA or invasive angiography), myocardial infarction and repeat revascularization within 2 years (+/- 3 months) after surgery;Perioperative outcome at 30 days.

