### Follow-up

Patients will receive cCTA examinations at 2 years (+/- 3 months) postoperatively. One week prior to the cCTA scan, blood samples (glomerular filtration rate, creatinine and thyroid stimulating hormone for the upcoming cCTA; LDL-cholesterol and HbA1c for follow-up) will be collected. At 30 days, 1 year, 2 years and 5 years postoperatively, phone calls will be used for follow-up (Table 1). cCTA should be performed within a time span of 6 months (-3 months to + 3 months) for 2 year’s cCTA. If cCTA or invasive angiography is performed for clinical reasons (e.g. signs of acute or chronic ischaemia, acute myocardial infarction, heart failure or recurrence of symptoms) prior to the above-mentioned time interval (> 3 months prior to the cCTA at 2 years) and the LITA graft is not occluded, cCTA will be performed according to protocol. If cCTA or invasive angiography is performed for other reasons prior to the above-mentioned time interval (> 3 months prior to cCTA at 2 years) and the LITA graft is occluded, cCTA will not be performed, and the findings of the cCTA/CAG will be used for statistical analysis. If CAG is performed for other reasons within the above-mentioned time intervals (≤ 3 months prior to the cCTA at 2 years) and the LITA graft does or does not show LITA graft occlusion, the cCTA will not be repeated, and the findings of the CAG will be used for statistical analysis. In the case of occlusion or dysfunction of other grafts rather than the LITA, patients with clinical symptoms and/or pathological findings noted from non-invasive testing should be referred for invasive angiography. This decision will be left to the clinical assessment of the participating centres.

**Table 1: ivae045-T1:** The follow-up process

Follow-up	30 days	1 year	2 years	5 years
Telephone interview	x	x	x (2 years + 3 months)	x
cCTA			x (2 years +/− 3 months)	

cCTA: coronary computed tomography angiography.

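### Any-form repeat revascularisation counts procedures prompted only by the protocol's 2-year cCTA, so an arm difference in silent LITA occlusion can leak into 5-year (and partly 2-year) MACE and LAD revascularisation

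*Protocol article*

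**What the plan says.** Under Outcome definitions, repeat revascularisation is "any form of repeat revascularization [CABG, percutaneous coronary intervention (balloon angioplasty or stent implantation)] after the index operation". Target vessel revascularisation uses the same wording, limited to procedures "to the LAD after the index operation". Neither carries a condition on symptoms, ischaemia or indication.

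The first definition feeds "MACE: composite outcome of all-cause death, myocardial infarction and repeated revascularization". Under Secondary outcomes this becomes "MACE-free survival (composite outcome of all-cause death, myocardial infarction and repeated revascularization) within 1 year, 2 years and 5 years after surgery", and the list also contains "Repeated revascularization of the left anterior descending artery (LITA target vessel revascularization) at 2 years and 5 years after surgery".

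The Follow-up section schedules a cCTA for patients at 2 years, with a window of 3 months either side. The cCTA section has two radiologists at each participating centre grade every graft. They are blinded to allocation. Two routes from the scan to an angiogram are described:

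- Follow-up, for grafts other than the LITA: "In the case of occlusion or dysfunction of other grafts rather than the LITA, patients with clinical symptoms" and/or pathological non-invasive findings should be referred, at the centre's discretion.
- cCTA section: "In cases with inconsistent results and if asked by the core centre, invasive angiography will be performed".

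For an agreed LITA occlusion in a patient without symptoms, the article neither prescribes nor prevents action. It does not say that results are withheld from treating clinicians, and it does not separate procedures that follow the study scan from the rest.

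**The concern.** The primary outcome is death or LITA occlusion, and most of its planned arm difference is occlusion. MACE is the outcome a reader will use to judge whether occlusion matters clinically. If a study scan uncovers a silent occlusion and a PCI follows for that reason alone, the imaging finding is counted again as a clinical event. More silent occlusions in one arm would then produce more MACE in that arm, even with equal rates of death, infarction and symptom-driven procedures.

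MACE is analysed as time to event, so a scan-prompted procedure would also end that patient's MACE follow-up. A later infarction or death would add nothing to the composite.

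The article already separates imaging done for clinical reasons from protocol imaging: it lists LITA occlusion on clinically indicated imaging as its own secondary outcome. Revascularisation has no matching distinction.

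**Working it through.** **Which outcomes are exposed.** The scan falls at 21 to 27 months.

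| Outcome | Exposure to scan-prompted procedures |
|---|---|
| 1-year MACE | None; it precedes the scan |
| 2-year MACE, 2-year LAD revascularisation | Partial: scans at 21–24 months with the procedure done by 24 months; later ones only if the +3-month window is applied |
| 5-year MACE, 5-year LAD revascularisation | Full |
| Death and infarction components | None |

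**Inputs from the Sample size section.** Death or occlusion at 2 years: 4% pedicled, 8% skeletonized. Deaths in the source data: 5/1014 = 0.49%. Patients per arm before the dropout allowance: 558. The stated hazard ratio reproduces: ln(0.96)/ln(0.92) = 0.49. The article gives no MACE or revascularisation rate, so there is no MACE figure to reproduce.

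**Assumptions.** f is the share of LITA occlusions that lead to a scan-prompted procedure: 10%, 25% or 50%. m is the true MACE risk, equal in both arms: 5%, 8% or 12%. None of these is in the documents.

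**Step 1: occlusion alone.** Pedicled 4% − 0.49% = 3.51%; skeletonized 8% − 0.49% = 7.51%.

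**Step 2: added procedures, x = f × occlusion.**

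| f | Pedicled | Skeletonized | Patients of 558 | Difference |
|---|---|---|---|---|
| 10% | 0.35% | 0.75% | 2.0 vs 4.2 | 0.4 points |
| 25% | 0.88% | 1.88% | 4.9 vs 10.5 | 1.0 points |
| 50% | 1.75% | 3.75% | 9.8 vs 20.9 | 2.0 points |

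**Step 3: observed MACE = 1 − (1 − m)(1 − x). Apparent HR = ln(1 − MACE skeletonized)/ln(1 − MACE pedicled).** For m = 8% and f = 25%, MACE is 8.8% pedicled and 9.7% skeletonized, so HR = 1.11. In full:

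| m | f = 10% | f = 25% | f = 50% |
|---|---|---|---|
| 5% | 1.07 | 1.17 | 1.30 |
| 8% | 1.05 | 1.11 | 1.20 |
| 12% | 1.03 | 1.07 | 1.14 |

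This table counts every scan-prompted procedure within the horizon.

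**Step 4: effect of the horizon.** Take occlusion of 3.5% vs 7.5%, 80% first found at the study scan and half of those revascularised (all assumed). Then x = 0.8 × 0.5 × 3.5% = 1.4% and 0.8 × 0.5 × 7.5% = 3.0%.

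- All counted on an 8% base: MACE 9.3% vs 10.8%, HR 1.17.
- Only half done by 24 months (x = 0.7% vs 1.5%), 8% base: MACE 8.6% vs 9.4%, HR 1.09.
- All counted at 5 years on an assumed 20% base: MACE 21.1% vs 22.4%, HR 1.07.

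The direction is the same throughout. The size depends on quantities that the documents do not give.

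**The case against.** The strongest reply is that counting every revascularisation is a defensible choice. It is objective and needs no adjudication, whereas a clinically driven label brings in a judgement on indication, possibly by clinicians who know the allocation. This stands, and it is why the any-form definition should not be replaced.

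Second, the Efficacy analysis section makes tests of secondary outcomes descriptive only. The primary test, its error rate and the sample size are untouched. This also stands and limits the weight of the point. A descriptive MACE hazard ratio will still be read as clinical support for the patency result.

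Third, whether the case report form records the indication belongs to a fuller document that is not shown. That is fair, so the point rests on the outcome definition that the article does state.

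A reader might go further in three ways that the text does not support:

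- **That all scan-prompted procedures enter 2-year MACE because the 2-year telephone call is at 2 years + 3 months.** A call date governs data collection. The MACE horizons are "within 1 year, 2 years and 5 years after surgery", with no window, while the imaging outcomes in the same list carry one. Events are timed by their date.
- **That the core-centre angiogram is a broad route to procedures.** It applies to inconsistent results and only on request, not to agreed occlusions.
- **That MACE can say nothing about clinical consequences.** Death and infarction are not scan-driven, 1-year MACE is clean, and revascularisation outcomes are also listed separately, so a reader can see part of what drives a difference. They cannot see which procedures were prompted by the scan.

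**Conclusion.** The point holds as a limited weakness of definition. As written, procedures prompted only by the study cCTA count in MACE and in LAD revascularisation, and nothing in the article separates them. Exposure is full at 5 years, partial at 2 years and absent at 1 year.

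With equal true risk, the apparent MACE hazard ratio is about 1.03 to 1.30 for f of 10% to 50% and base MACE of 5% to 12%. It falls to about 1.09 or 1.07 in the examples that allow for the 24-month cut-off or a larger 5-year base. These values also rest on the planned 4% vs 8% difference being real. They ignore silent occlusions that would later have been treated for symptoms anyway, which would shrink the excess at 5 years. No single value should be taken as an estimate. The case is for a cheap improvement in what the trial can conclude, not for a correction to its primary analysis.

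**What to change.** Keep the any-form definitions of repeat and LAD revascularisation, and add:

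1. For each revascularisation, record prospectively whether it was triggered by symptoms, documented ischaemia or infarction, or only by study imaging (the protocol cCTA or an angiogram requested because of it). Classify the trigger blind to arm where possible.
2. Pre-specify a supplementary analysis of MACE and LAD revascularisation at 2 and 5 years that counts only clinically driven procedures, shown beside the any-form result.
3. Report the number of scan-prompted procedures by arm.

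The cost is one extra case report form field, a judgement on indication, and fewer events in the supplementary analysis. It is best settled before the first 2-year scans, because the trigger may be hard to reconstruct from a telephone interview at 5 years. Patient care, sample size and the primary analysis are unchanged.

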## STATISTICS

### Study design and objectives

This is a 2-arm, prospective, randomized, observer-blinded, multicentre clinical trial, designed to evaluate the impact of harvesting technique of LITA on graft occlusion-free survival. The primary end point is defined as death or LITA graft occlusion identified via cCTA or invasive angiography within 2 years (+/− 3 months). The secondary end points include MACE- (composite outcome of all-cause death, myocardial infarction and repeated revascularization) free survival, occlusion rate and other graft-related outcomes. LITA graft occlusion-free survival and MACE-free survival are treated as time-to-event variables with observation time ranging from date of surgery (time zero) to either date of event or censoring date.

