## OUTCOME MEASURES

### Primary outcome

Death or LITA graft occlusion in cCTA or invasive angiography within 2 years (+/- 3 months) after surgery.

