### Efficacy analysis

The primary end point of LITA graft occlusion-free survival will be compared between the 2 treatment groups using Kaplan–Meier graphs and a centre-stratified two-sample log-rank test. In addition, Cox proportional hazards regression analysis adjusting for clinically relevant confounders, will be performed. Hazard ratios and their 95% confidence intervals will be estimated.

The primary efficacy hypotheses will thus be formulated as:H_0_: hazard ratio_skeletonized vs pedicled_ = 1H_1_: hazard ratio_skeletonized vs pedicled_ ≠ 1

The primary efficacy analysis will be performed in the modified intention-to-treat population population.

MACE-free survival and other secondary end points that follow the time-to-event format will be analysed with Kaplan–Meier test,log-rank test and Cox proportional hazards regression analysis. Categorical end points will be compared between treatment groups using the χ^2^ test. *P*-values < 0.05 will be considered statistically significant; however, formal significance testing will be applied to the primary hypothesis only. Statistical tests for secondary end points will be applied in a descriptive manner only.

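### Occlusion is looked for on schedule only once, between 21 and 27 months, so Kaplan-Meier curves on event dates will not show the 2-year event rates; the log-rank test is at risk only under further conditions

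*Protocol article*

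**What the plan says.** The primary outcome is "Death or LITA graft occlusion in cCTA or invasive angiography within 2 years (+/- 3 months) after surgery" (Protocol article, Primary outcome).

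On imaging, the Follow-up section states: "Patients will receive cCTA examinations at 2 years (+/- 3 months) postoperatively". The window is six months wide: "cCTA should be performed within a time span of 6 months". The other contacts are by telephone: "At 30 days, 1 year, 2 years and 5 years postoperatively, phone calls will be used for follow-up". Table 1 places the 2-year call at 2 years + 3 months, the end of the scan window. Earlier imaging happens only when there is another reason for it; the rule begins "If cCTA or invasive angiography is performed for clinical reasons".

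On analysis, Study design and objectives gives one handling for this end point and for the MACE outcome: "treated as time-to-event variables with observation time ranging from date of surgery (time zero) to either date of event or censoring date". Efficacy analysis says that the primary end point is "compared between the 2 treatment groups using Kaplan–Meier graphs and a centre-stratified two-sample log-rank test", with Cox hazard ratios in addition. The article does not say how an occlusion first seen on the scan is dated, or when a patient with a patent graft is censored.

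**The concern.** A telephone call cannot reveal a silent occlusion. Unless symptoms lead to earlier imaging, all that is known is that the graft closed some time between surgery and the scan. Such a time is interval-censored, and the date that enters the analysis is the scan date. Kaplan-Meier, log-rank and Cox are designed for right-censored times with observed event dates.

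Two things are at stake. First, the plotted event-free proportions may not be the 2-year rates that readers will take them for. Second, the test and hazard ratio could pick up a difference in scan timing between the arms.

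The ± 3 months also leaves the horizon for deaths open: it is unclear whether a death at 25 months counts when the scan at 22 months showed a patent graft.

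**Working it through.** **1. The plan's own figure (Sample size rationale).** Inputs: 4% pedicled and 8% skeletonized at 2 years, two-sided alpha 0.05, power 0.80.
- HR = ln(0.96)/ln(0.92) = 0.49, as stated; the inverse is 2.04.
- Schoenfeld events: 4 × (1.960 + 0.842)² / (ln 0.49)² ≈ 62, as stated.
- Freedman events: (1.960 + 0.842)² × (1.49/0.51)² ≈ 67; 67/0.12 ≈ 558 per arm, as stated.

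The design thus reproduces, and it rests on 2-year proportions.

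**2. Share of events without an observable date.** The source data had 21 + 25 = 46 occlusions and 5 deaths: 46/51 = 90%. On the planning rates, 5/1014 = 0.5% deaths out of an average 6% leaves 5.5/6 = 92% occlusions. The share found early on symptom-driven imaging is not given.

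**3. Curves, patent grafts censored at scan.** Assumptions: scans uniform over 21–27 months; all occlusions present by month 21; 25% of them found early; 0.5% deaths in each arm. Occlusions are then 3.5% and 7.5%.
- Found early: 0.875% and 1.875%. Deaths by month 21: 0.5 × 21/24 = 0.44%. Event-free at 21 months: about 0.987 and 0.977.
- Share of those reaching the window who are occluded at scan: h = 2.625/99.125 = 0.0265 and 5.625/98.125 = 0.0573.
- Scans empty the risk set evenly, so S(t) = S(21) × [(27 − t)/6]^h.
- At 24 months: 1 − 0.987 × 0.5^0.0265 = 3.1% and 1 − 0.977 × 0.5^0.0573 = 6.1%. Simulation, which includes deaths in the window, gives about 3.2% and 6.2%.
- At 27 months the last steps fall on a handful of patients; simulation with 558 per arm gives means of about 18% and 34%.

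**4. Curves, patent grafts carried to 27 months.** At 24 months only half of the scan-detected occlusions have been dated: 0.875 + 2.625/2 + 0.5 = 2.7% and 1.875 + 5.625/2 + 0.5 = 5.2%. The 27-month value is right.

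Kaplan-Meier readings when the early share is varied (simulation, true 4%/8%):

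| Found early | Censored at scan, 24 mo | Censored at scan, 27 mo | Carried to 27, 24 mo |
|---|---|---|---|
| 10% | 3.0% / 5.8% | 20.8% / 38.9% | 2.4% / 4.6% |
| 50% | 3.4% / 6.8% | 13.5% / 26.5% | 3.1% / 6.1% |

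**5. Log-rank and hazard ratio (simulation, 558 per arm).**
- Same timing in both arms, censored at scan: HR 2.02–2.04, type I error 5.1%, power 78.5–81% (status comparison 81–82%).
- Timing differs by arm, one common censoring date at 27 months: HR 1.00–1.01 and about 5–6% rejection under no effect.
- Timing differs by arm, censored at scan, no true effect (6% each), false rejection:

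| Shape of the shift | Found early | 2 weeks | 1 month |
|---|---|---|---|
| Whole window slid earlier | 25% | 18% | 40% |
| Whole window slid earlier | none | 27% | 64% |
| Inside the window, bell-shaped | 10% | 33% | 83% |
| Inside the window, bell-shaped | 50% | 13% | 34% |

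With 25% found early and scans kept inside the window, a 2-week shift gives about 13% (flat shape) to 26% (bell shape); with more found early and a flat shape it falls to about 8%. A comparison of 2-year status stays near 5% throughout.

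**6. Sample size for 2-year status.** n = [1.960 √(2 × 0.06 × 0.94) + 0.842 √(0.04 × 0.96 + 0.08 × 0.92)]² / 0.04² = 552.2, so 553 per arm. Power is 80.4% at 558 and 87.3% at 675 per arm.

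**The case against.** The strongest reply has four parts.

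- *The test may be sound.* A reader might infer from the mismatch that the log-rank test and hazard ratio are invalid, or valid only with identical scan timing. The article does not support that. Bias needs both censoring at the scan and timing that differs by arm. The article states neither, and nothing in Follow-up gives the arms different schedules. Table 1's call at 2 years + 3 months could serve as a common censoring date, which removes the distortion. This stands. The article does not, however, make that link, and it describes blinding only for observers and image readers, so the harmful combination is not excluded either.
- *Censoring rules belong in the analysis plan.* True for the detail. But the article itself fixes dated time-to-event methods for the primary end point, and the curves miss the 24-month rates under either censoring rule. That is a mismatch between stated method and stated schedule, not an omitted detail.
- *The sizes rest on assumptions.* This stands. Uniform timing and the 25% share are not in the article, sliding the window earlier puts some scans outside the permitted months, and the 27-month figures come from a nearly empty risk set. At 24 months the ratio of the two curves is roughly preserved (6.2/3.2 = 1.9).
- *Fixed-time status is analysed anyway.* Occlusion at 2 years is a secondary outcome and categorical end points get a χ² test. This helps, but that analysis is descriptive and leaves out deaths.

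**Conclusion.** The mismatch is real and should be fixed. About nine in ten expected events are occlusions, and those first seen on the scheduled scan carry only an appointment date. The planned Kaplan-Meier curves would then not estimate the 4% and 8% on which the trial is sized: about 3.2%/6.2% at 24 months and 18%/34% at 27 months with censoring at scan, or about 2.7%/5.2% at 24 months with a common date at 27 months. These figures assume uniform scan timing and 25% early detection; the direction holds from 10% to 50%. No imbalance between the arms is needed.

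The threat to the log-rank test and hazard ratio is conditional. Where both conditions hold, a 2-week difference might give about 18% false rejection and 1 month about 40%; for 2 weeks inside the window, about 8–26% is a fair illustration, and more if few occlusions are found early. Confidence is high on the mismatch and the curves, and much lower on any particular error rate.

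**What to change.** Define the primary end point as status at 2 years: death by one fixed day (for example the end of the scan window, which matches the 2-year call in Table 1), or occlusion on the 2-year scan or any earlier imaging. Compare the arms with a centre-stratified Mantel-Haenszel test and report a risk difference with 95% CI. Treat living patients without a scan as having missing status, not a patent graft, for example by multiple imputation with best- and worst-case bounds. Keep a time-to-event analysis as sensitivity, either interval-censored or a log-rank test with one common censoring date. If the log-rank test is kept as primary, stating that common date and a rule for unscanned patients is the minimum; the 24-month curve would still read low.

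The cost is wording in Primary outcome, Study design and objectives, Sample size rationale and Efficacy analysis, to be settled before outcomes are known. No new patients or data are needed, and power is unchanged. The downside is that the headline effect becomes a risk difference or ratio instead of a hazard ratio.
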